**Table 10. Classification of AEs**

| AE Classification | AE Categories                                                                                                                 |
|--------------------------|--------------------------------------------------------------------------------------------------------------------------------------|
| Severity                 | Mild/Moderate/Severe/Life threatening                                                                                                |
| Serious                  | Yes / No                                                                                                                             |
| Relationship             | Certain/Probable/Possible/Unlikely                                                                                                   |
| Action taken             | Permanently discontinued/Stopped temporarily/Dose reduced/ Dose increased/ No action taken/ Unknown                                  |
| Outcome                  | Recovered or resolved / Recovering or resolving / Not recovering or resolved / Recovered or resolved with sequelae / Fatal / Unknown |

## EVG001SAH Statistical Analysis Plan

Drug related events will be defined as ones whose relationship is given as certain, probable or possible. Any events with missing relationship to study drug will be tabulated as related. Any events with missing intensity will be tabulated in a separate category. If a patient has an AE which changes in severity this will be recorded as a separate occurrence of the same event. Serious adverse events (SAEs) are classified as described in the protocol. If a patient has more than one occurrence of the same AE and at least one is considered drug-related, the patient will be included as having a drug-related AE for that AE preferred term. Similarly, if a patient has more than one occurrence of the same AE and they have different severities, they will be summarised at the worst severity for that AE preferred term.

When summarising the time to onset of an AE the day of first dose will be used throughout as a reference point. If only a month is provided for date of onset, a conservative approach will be followed and events will be assumed to start at max(date of first dose, first day of the month). Likewise, if only a month is provided for the end date, the event will be assumed to have resolved at min(last date of month, date of onset for a new occurrence of the same AE for that patient).

For laboratory data all numeric blood results are classified by the investigator as Clinically Significant / Not Clinically Significant. All categorical urine results are classified as Clinically Significant (Yes / No). All blood and urine samples taken for safety evaluations are assayed by the local laboratory at each hospital. Data will be pooled across centres and summarised by treatment arm despite any differences in reference ranges.

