### *Statistical Analysis Plan:*

A Phase II Safety, Tolerability, Pharmacokinetic and Pharmacodynamic Study of SFX-01 in Subarachnoid Haemorrhage, with exploratory efficacy evaluations. The study is a randomised, double-blind, parallel-group design comparing SFX-01 (300 mg) taken orally as capsules or as a suspension via a nasogastric tube (NG) twice-daily for up to 28 days versus placebo in 90 patients who have had SAH and present within 48 hours of ictus.

|                            |                                                                        |
|----------------------------|------------------------------------------------------------------------|
| Sponsor:                   | Evgen Pharma plc                                                       |
|                            | [name]
[name]
Liverpool
[name] |
| Author &
Qualifications | [name] M.Sc. C.Stat.                                             |

|                 |                  |
|-----------------|------------------|
| Document Date:  | 04 February 2019 |
| Version/Status: | Final            |

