### **5.13 Safety Data**

Recording of AEs starts from informed consent and continues until at least 30 days post last dose. The definition of AEs and SAEs are given in the protocol.

Adverse events starting on or after the first treatment dose are therefore defined as Treatment Emergent Adverse Events (TEAEs). Any AE that starts more than 30 days past last dose and is considered to be at least possibly related to study treatment should also be defined as a TEAE. Any event starting before the first dose of study drug is identified as a Pre-Treatment Adverse Event (PTAE). Any event starting before the first dose of study drug that subsequently worsens is also be defined as a TEAE.

All events are coded using the MedDRA dictionary. The actual description of the AE is matched, as closely as possible, with the Lower Level Term in the dictionary.

All AEs are classified as described in Table 10.

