## EVG001SAH Statistical Analysis Plan

An overview table of the number and percentage of patients with any Pre-Treatment Adverse Event (PTAE), TEAEs, Deaths, Serious TEAEs, All Serious AEs, TEAEs leading to discontinuation, maximum severity of TEAEs and Drug-Related TEAEs will be presented as a categorical summary according to treatment arm and overall. In the maximum severity row, patients will be counted once according to the worst severity categorized as missing/mild/moderate/severe/life threatening.

The following summarized of AEs will be produced:

- number and percentage of patients with at least one PTAE by Preferred term
- number and percentage of patients with at least one TEAE by Preferred term
- number and percentage of patients with at least one TEAE by Preferred term by maximum severity
- number and percentage of patients with at least one TEAE by Preferred term that is related to study drug
- number and percentage of patients with at least one TEAE by Preferred term that is serious
- number and percentage of patients with at least one adverse event that is serious, to include any serious AEs that occurred prior to dosing with study medication
- number and percentage of patients with at least one TEAE by Preferred term that lead to discontinuation of treatment corresponding to events where action taken with study treatment is 'Permanently discontinued'

In each table events will be grouped according to SOC and within each SOC events will be presented in order of decreasing frequency. The SOC row will present the number of patients with at least one TEAE within that SOC for the subset of events being summarized.

Serious TEAEs will be listed by patient and treatment arm, indicating the name of the AE, PT and SOC, together with details of the start and end dates, event duration (days) and maximum intensity. Additionally, the relation to study drug, action taken, outcome and the date of the first dose of study drug will also be displayed.

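### The rule for month-only AE onsets can never give a pre-dose date, so events shown by their own record to predate dosing are dated to first dose or later

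*SAP*

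**What the plan says.** All the relevant rules are in SAP Section 5.13 (Safety Data), and the outputs are in Section 7 under Adverse Events.

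- Collection: "Recording of AEs starts from informed consent and continues until at least 30 days post last dose". Events before dosing are therefore in the database by design.
- Classification: "Adverse events starting on or after the first treatment dose are therefore defined as Treatment Emergent Adverse Events (TEAEs"), and "Any event starting before the first dose of study drug is identified as a Pre-Treatment Adverse Event (PTAE"). A pre-dose event that later worsens also counts as treatment-emergent.
- Missing onset day: the SAP describes its handling as conservative. When the record gives the month alone, "events will be assumed to start at max(date of first dose, first day of the month"). The only trigger is that the day is missing. No exception is made for an earlier month or for a known end date.
- Missing end day: "the event will be assumed to have resolved at min(last date of month, date of onset for a new occurrence of the same AE for" the patient concerned). This end date is not tied to the imputed start or to first dose.
- Outputs: Section 7 tabulates pre-treatment events separately ("number and percentage of patients with at least one PTAE by Preferred term"), next to the tables of treatment-emergent, serious and drug-related events. It also lists serious treatment-emergent events with start date, end date and duration.

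**The concern.** The imputation works when the onset month contains or follows first dose. In the first case the timing is unknown and the event is cautiously treated as on-treatment. In the second the first of the month is already after dosing. The rule has no boundary on the other side. Where the recorded month, or a complete end date, shows that the event began before dosing, the formula still moves the onset to first dose or later. Calling this conservative justifies resolving an ambiguous onset against the drug. It does not justify overriding a record that settles the question.

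Safety is the first primary objective listed in Section 2. An affected event would carry a false onset date. If classification follows that date, the event would also leave the pre-treatment table and enter the treatment-emergent tables. A serious event could then appear in the listing with a start later than its end. Section 5.13 also tabulates a missing causality assessment as related, so such an event could be counted as drug-related.

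**Working it through.** The plan gives no figure to reproduce, so the check applies the rule as written to worked dates.

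**Inputs.** Imputed start S = max(D, M), where D is the date of first dose and M is the first day of the recorded month. The event is treatment-emergent if S ≥ D and pre-treatment if S < D (both from Section 5.13).

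**Step 1: what the formula can return.** S = max(D, M) ≥ D for every D and M, so S < D is impossible. Enumerating every first-dose day in a year against every onset month gives 365 × 12 = 4,380 combinations, and 0 of them return a pre-treatment start.

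**Step 2: worked records.** The last column shows the class if S is used for classification.

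| Onset | End | First dose | S under the SAP rule | Known to predate dosing? | Class |
|---|---|---|---|---|---|
| Feb | unknown | 2 Mar | max(2 Mar, 1 Feb) = 2 Mar | Yes, month is over | Treatment-emergent |
| Feb | 1 Mar | 2 Mar | 2 Mar, after the end | Yes | Treatment-emergent |
| Mar | 14 Mar | 15 Mar | max(15 Mar, 1 Mar) = 15 Mar, after the end | Yes, end precedes dose | Treatment-emergent |
| Feb | Feb | 1 Mar | 1 Mar; end imputed as the last day of Feb or earlier | Yes | Treatment-emergent |
| Mar | 20 Mar | 15 Mar | 15 Mar | No, ambiguous | Treatment-emergent |
| Apr | unknown | 15 Mar | max(15 Mar, 1 Apr) = 1 Apr | No, after dose | Treatment-emergent |

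The first four rows are wrong and the last two are as intended. In the third row, end minus start is 14 − 15 = −1 day. In the fourth, the SAP's own start and end rules contradict each other.

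**Step 3: how often a month boundary can matter.** The SAP does not give the interval between consent and first dose, so the gaps here are assumptions. For a gap of h hours, the chance that a month end falls inside it is about (h/24)/30.4:

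- 12 h: 0.5/30.4 = 1.6%
- 24 h: 1/30.4 = 3.3%
- 48 h: 2/30.4 = 6.6%

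These are chances of a boundary, not shares of patients affected. To reach the latter, each must be multiplied by the chance that the patient has a pre-dose AE and by the chance that its onset lacks a day. Neither is given and both are at most 1, so the percentages are upper bounds under the assumed gaps. They cover only events whose recorded month is over before dosing. The end-date case (third row) needs no month boundary and cannot be sized from the SAP.

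**Step 4: the proposed condition.** With the rule limited as set out in the fix, the first four rows become pre-treatment (provided the event does not later worsen) and the last two are unchanged.

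**The case against.** The strongest objection is about scope. The imputation sentence follows one about summarising time to onset, while pre-treatment and treatment-emergent status is defined earlier in the section by when the event actually starts. Read that way, an event known to predate dosing stays pre-treatment and the imputed date serves only the timing summaries. This stands in part: a reader might infer that the SAP certainly moves such events into the treatment-emergent tables, and the document does not state that. But it does not confine the rule to timing summaries either, and it gives no other way to classify an event with a missing day. Even on the narrow reading, the onset is misdated and may fall after the event's own end.

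The second objection is about consequence, and most of it stands.

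- The title describes patients enrolled "in 90 patients who have had SAH and present within 48 hours of ictus", so the time between consent and dosing is probably short and spent in hospital, where a missing day is least likely. Month-only dates are more plausible in later follow-up, where the rule works.
- Section 7 includes a table of all serious events, pre-dose ones among them, and that count does not change.
- Table 11 plans no formal test on AEs, and the rule is the same in both arms of a double-blind trial. A reader might infer a biased comparison of arms; nothing in the SAP shows one.
- Any error adds to the treatment-emergent count, which is the cautious direction.

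Third, an ongoing event from an earlier month may worsen after dosing and then be properly treatment-emergent. Misclassification is therefore not certain for every such record, and any correction must keep that clause. It cannot rescue an event that ended before dosing.

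**Conclusion.** The rule is wrong as written, in a minor way. Without further assumption, it gives any month-only event known to predate dosing an onset on or after first dose, in some cases later than its own end. That the event is then counted as treatment-emergent, against the SAP's own pre-treatment definition, depends on the imputed date being used for classification. This is the likely reading but not a stated one.

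The number of events is probably small and cannot be calculated from the SAP. It would be a mistake to read the month-boundary range of roughly 2% to 7% as the proportion of patients affected: it is at most a ceiling for one of the two cases, under assumed gaps of 12 to 48 hours. The trial's conclusions are not at risk. The point is worth making because the correction costs almost nothing and removes a contradiction within one section.

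**What to change.** Add a condition to the month-only onset rule in Section 5.13:

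- Use the later of first dose and the first of the month only when the recorded month is the month of first dose or later and no end date, recorded or imputed, precedes first dose.
- Otherwise impute the later of the first day of the recorded month and the consent date, and classify the event as pre-treatment, subject to the existing clause that a pre-dose event which subsequently worsens is also treatment-emergent.
- State that the imputed date is used for classification as well as for time to onset.

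Ambiguous onsets remain treatment-emergent, so the cautious intent is kept. The cost is a sentence or two in the SAP and one programming condition. No new data should be needed, since Section 7 already lists consent and dosing among the dates to be reported. If the change comes after database lock and unblinding, Section 1 requires it to be documented and justified in the clinical study report.

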#### **5.14 Pharmacokinetic Data**

No derived parameters for CSF and blood HP and MDA concentrations will be created. The method of analysis and presentation is described in a later section. This also applies to Sulforaphane (SFN) and SFN metabolite concentrations at Day 7 from patients who do not take part in the sub-study.

For patients entering the sub-study, SFN parent drug and metabolite concentrations are measured serially in both CSF and blood samples obtained pre-dosing and then hourly for up to 6 hours in a subset of 12 EVD patients on one of the first 3 doses and at Day 7. PK parameters for both CSF and blood will be derived for each individual patient using the concentrations over time profiles, data permitting. Full details of the pharmacokinetic analyses will be provided separately.

#### **5.15 Time-Windows**

The protocolled defined visit windows for assessments are +/-1 for Day 7, -2 at Discharge, -6/+2 at Day 28, +/-14 at Day 90 and +/-28 at Day 180. However, for the purpose of any timepoint analyses, data will be included at the visit closest to the time the recordings were taken.

## 6 Statistical Methods

### 6.1 General Considerations

All data will be described and analysed according to treatment arm (SFX-01, Placebo) and day and time of assessment (if appropriate), for each patient population (PP, ITT, Safety, sub-study PK).

A (two-sided) significance level of 5% ( $<0.05$ ) will be implemented throughout. The null hypothesis assumed throughout is that there is no difference between the active treatment and the control for any comparison performed (SFX-01 vs Placebo).

Part way through the trial the randomization was amended to stratify by WFNS score (1-3 v 4-5) and centre. For purposes of analyses that are stratified, WFNS score will be taken from the CRFs for patients randomized prior to the amendment and from the random scheme for patients randomized after the amendment.

### 6.2 Analysis Methods

Each endpoint subject to formal statistical analysis is listed in Table 11. To investigate the robustness of the primary analysis of each endpoint additional analyses will be performed. These are described as sensitivity analyses if they assess whether the results are influenced by departures from assumptions made in the primary analysis and are described as supplementary analyses if they assess a closely related measure not considered as important as the one chosen in the primary analysis.

**Table 11. Formal statistical analyses to be conducted and pre-planned supplementary and sensitivity analyses**

| Endpoint                     | Notes                                                                                                                                                                                                                                                                                                                                                                                                                                                                                                                                                   |
|------------------------------|---------------------------------------------------------------------------------------------------------------------------------------------------------------------------------------------------------------------------------------------------------------------------------------------------------------------------------------------------------------------------------------------------------------------------------------------------------------------------------------------------------------------------------------------------------|
| TCD                   | 
Primary: maximum post-dose MCA mean flow velocity
 
Sensitivity analysis:
 
 
Removing baseline data from the analysis model if it appears SFX-01 has had an effect by Day2
 
 
Supplementary analyses:
 
 
Mean of 3 largest post-dose MCA mean flow velocities
 
Maximum post-dose Lindergaard ratio
 
Maximum MCA mean flow velocity per timepoint
 
Mean effect over days 5 to 9 of maximum MCA mean flow velocity.
 
 |
| Modified Rankin Scale | 
Analysis at Day 7, 28, 90 and 180 and at discharge
 
Sensitivity analysis:
 
 
If more than 15% of patients have missing data at Day 180 in either treatment arm, the analysis at each timepoint will be repeated by carrying forward the
 
                                                                                                                                                                                                                                                     |

## EVG001SAH Statistical Analysis Plan

|                                         |                                                                                                                                                                                                                                                                                                                                                                    |
|-----------------------------------------|--------------------------------------------------------------------------------------------------------------------------------------------------------------------------------------------------------------------------------------------------------------------------------------------------------------------------------------------------------------------|
|                                         | outcome from the most recent timepoint with recorded data..                                                                                                                                                                                                                                                                                                        |
| Glasgow Outcome Score - Extended | Analysis at Day 28, 90 and 180

Sensitivity analysis: 
 
If more than 15% of patients have missing data at Day 180 in either treatment arm, the analysis at each timepoint will be repeated by carrying forward the outcome from the most recent timepoint with recorded data..
 
                               |
| Delayed Cerebral Ischaemia       | Proportion of patients with an event                                                                                                                                                                                                                                                                                                                               |
| New Cerebral Infarct             | Proportion of patients with an event                                                                                                                                                                                                                                                                                                                               |
| Triple H Therapy                 | Proportion of patients with hypertensive (Triple H) therapy                                                                                                                                                                                                                                                                                                        |
| SF-36                            | Physical and Mental Health scores at Day 28, 90 and 180.

Sensitivity analysis: 
 
If more than 15% of patients have missing data at Day 180 in either treatment arm, missing data diagnostics performed.
 
                                                                                                     |
| CLCE-24                          | Score based on the percentage of Cognitive and Emotional questions at Day 90 and 180 that indicate problems that severely hinder daily life

Sensitivity analysis: 
 
If more than 15% of patients have missing data at Day 180 in either treatment arm, missing data diagnostics performed.
 
                  |
| BICRO-39                         | Primary: overall BICRO score at Day 90 and 180

Supplementary analyses: 
 
8 subscale scores at Day 90 and 180
 
 Sensitivity analysis: 
 
If more than 15% of patients have missing data at Day 180 in either treatment arm, missing data diagnostics performed.
 
 |
| SAHOT                            | SAHOT category at Day 28, 90 and 180

Sensitivity analysis: 
 
If more than 15% of patients have missing data at Day 180 in either treatment arm, missing data diagnostics performed
 
                                                                                                                          |
| Length of Acute Hospital Stay    | Primary: including patients who die prior to discharge censoring them 1 day longer than the largest observed stay

Sensitivity analysis; 
 
Censoring at the date of death as end of hospital stay for patients who die prior to discharge
 
                                                                    |
| Blood & CSF HP and MDA       | Blood concentrations of HP & MDA at Day 7 and D28
CSF concentrations of HP & MDA at Day 7                                                                                                                                                                                                                                                                       |

Analyses of the TCD, mRS and GOSE endpoints will be performed in both the PP and ITT populations with the PP population considered as primary. Other endpoints will initially only be analysed in the PP population and will only be analysed in the ITT population if there is a meaningful discrepancy in the results of endpoints analysed in both populations.

